#### Qualitative outcomes

The use of SeMaS will be evaluated with the professionals in the intervention arm by semi-structured interviews. Informed consent for these interviews will be obtained. Questions for the interview will be formulated using the barriers and facilitators on different levels of healthcare [38]. Special attention will be paid to the usefulness of the instrument in actual practice and the additional value for improvement of self-management of patients and the creation of individual care plans. The purposive sample size will be determined based on theoretical saturation. Therefore, data review and analysis will be done in conjunction with data collection.

### Sample size

Sample size calculations have been made using the results from three studies on the primary outcome measure, PAM-13 [17,34,39]. In these studies, improvements in PAM scores after intervention vary from 4% to 8% (SD 12 to 17). Based on these studies, we expect to find a difference in PAM score of 6% (SD 14.0) in this study. For the power calculations, we assume an intraclass correlation coefficient (ICC) of 0.05 based on the article of Campbell *et al*. [40]. This article states that an ICC of 0.0 to 0.5 is normal for outcomes in primary care research. To reach a power of 80% and alpha of 0.05, and considering ICC of 0.05, at least 25 patients per practice are needed when using 15 practices. With an expected dropout rate of 33%, 33 patients would be needed per practice, thus, 495 in total. Our secondary outcomes comprise lifestyle measures that will not be applicable to every patient, such as smoking. Therefore, we strive to include 50 patients per practice. Thus, 750 patients will be included in total.

### Analysis

We made an *a priori* analysis plan for the primary analysis of the data, including details about the primary and secondary outcomes, covariates, treatment of missing values, and planned analyses. The outline of the analysis plan will be described here. The primary analysis will be an intention-to-treat analysis to test the hypothesis that patients who received personalized self-management support will be more activated than patients who did not receive personalized self-management support, expressed by the PAM-13 score. Secondary analyses will test the hypothesis that patients who received personalized self-management support will be more able to change their lifestyle in a positive way than patients who did not receive personalized self-management support, as measured with the RAPA, REAP-S and 10-item Behavior Change Consortium questionnaire.

Using analysis of covariance (ANCOVA) (that is, multilevel linear regression with the follow-up score as the outcome and the baseline score as a covariate), the difference in scores on PAM-13 in the subgroups at T = 0 and T = 6 months will be examined in the control and intervention arm. Subsequently, we will analyze the impact of the intervention on predefined subgroups as measured by the SeMaS. We defined three subgroups: patients who are ready for self-management, patients who can undertake self-management with minor barriers, and patients with severe barriers to self-management, by calculating an overall score on the SeMaS questionnaire.

Each secondary outcome will be analyzed with a multilevel multivariate covariance regression model, with the analyst blind to practice allocation to trial arms. Covariates that will be controlled for are: age, gender, chronic condition (from the medical-record data), social support (as measured with the SeMaS), diagnosis of depression based on the International Classification of Primary Care (ICPC) code and health literacy (as measured with the Short Test of Functional Health Literacy in Adults (S-TOFHLA)) [41,42], and the baseline scores. All statistical analyses will be performed using SPSS software (version 20, IBM Corp.), SAS (version 9.2, SAS Institute Inc.) or MLWIN (version 2.28, University of Bristol).

We will also perform a per protocol analysis of data from patients who received a referral to a self-management intervention. We will examine adherence to the self-management intervention program, comparing patients from intervention practices with control. Also, we will test the effect of the intervention on process outcomes (filled in individual care plans, the number of referrals to self-management interventions, and the number of consultations in the general practice and emergency care) using multilevel multivariate regression techniques.

The effect of cluster will be determined by performing a multilevel regression analysis without explaining variables. With this analysis, we can determine the variance at the different levels. Subsequently, we can determine the intraclass correlation of this study:

ICC=Clustervariance/Clustervariance+Patients'variance

We will qualitatively analyze the interviews with healthcare professionals. The interviews will be transcribed verbatim. The transcripts will be analyzed by open coding at macro level using predefined main codes according to the barriers and facilitators at different levels of healthcare, as proposed by Grol and Wensing [38]. These levels are: innovation, individual professional, patient, social context, organizational structure, and economical and political context. After the open coding, the research team will group themes and subthemes for each level of healthcare. The program Atlas.ti (version 6, ATLAS.ti Scientific Software Development GmbH) will be used for analysis.

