All 15 general practices of the DOH will participate in the trial. We recruited the practices through the DOH cooperation. The practice nurses will receive training in working with the SeMaS. As mentioned, we will perform randomization at the cluster level. Furthermore, as the ability of the practice nurse to influence the self-management behavior of the patient can affect the study results, we dichotomized practices into two equal groups using the percentage of practice nurses in the practice that participated in the behavioral change training [29]. Also, practices were dichotomized in two equal groups using the volume of practice nurses corrected for practice size, as the workload can affect the study results as well. This resulted in four strata. For each stratum, a separate two-block randomization list was produced to randomize the practices to the control or intervention arm [33]. Two practices were coupled in the randomization procedure to prevent contamination, because one practice nurse worked in both practices. The final allocation of practices is shown in Table 1.

**Table 1 T1:** Randomization strata and the number of practices per stratum of the SeMaS study

	**Low participation in behavioral change training**		**High participation in behavioral change training**	
	**Intervention**	**Control**	**Intervention**	**Control**
Low volume of practice nurses	2	1	2	2
High volume of practice nurses	1	3	2	2

Volume of practice nurses: the number of full time equivalents divided by the number of patients in the practice. Participation in training: percentage of the practice nurses who attended the training for behavioral change to enhance self-management that was provided in 2011 [29]. SeMaS, self-management screening questionnaire.

A representative of the care group DOH consented with participation in the study for all practices. After performing the randomization procedure, we informed the practices about participation in the study.

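### The primary PAM-13 model and the listed secondary models leave out both factors the practices were stratified on, and the allocation is uneven on one of them, nurse volume

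*Protocol article*

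**What the plan says.** Under Practices, the protocol article splits the practices in two by the share of nurses who attended the behavioural-change training, "as the ability of the practice nurse to influence the self-management behavior of the patient can affect the study results". It splits them again by nurse volume corrected for practice size, "as the workload can affect the study results as well". "This resulted in four strata", and randomisation followed them: "For each stratum, a separate two-block randomization list was produced to randomize the practices".

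Under Analysis, the primary PAM-13 model is "multilevel linear regression with the follow-up score as the outcome and the baseline score as a covariate". No other covariate is named for it. For the secondary outcomes the article gives a list: "Covariates that will be controlled for are: age, gender, chronic condition (from the medical-record data), social support (as measured with the SeMaS"), then depression diagnosis, health literacy, "and the baseline scores". Neither training participation, nor nurse volume, nor a stratum term appears.

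Table 1 gives intervention:control counts of 2:1 (low training, low volume), 1:3 (low training, high volume), 2:2 (high training, low volume) and 2:2 (high training, high volume).

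**The concern.** The design section treats the two factors as prognostic and the stated models then ignore them. Two things follow if the design section is right.

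First, stratification did not secure balance on nurse volume, so only the model can correct what is left. Adjusting for baseline PAM-13 helps to the extent that the factor already shows in baseline scores. It does not help where nurse workload acts on change during follow-up, which is a natural reading of the article's reason for stratifying.

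Second, a model that omits factors used in the randomisation leaves the variance they explain in the residual between practices. With 15 practices that residual is the larger part of the error, so the standard error is overstated when the factors matter. The main loss is power; the test becomes conservative rather than liberal.

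**Working it through.** **Inputs.** From Sample size: a difference of 6 (read as PAM points), SD 14, ICC 0.05, power 80%, alpha 0.05 (taken as two-sided), 25 evaluable per practice, 15 practices, a target of 50 per practice, dropout 33%. From Table 1: the eight cell counts. Assumed, because the documents give no figure: the size b of a nurse-volume effect, and the share of between-practice variance that the factors explain.

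**The plan's own figure.** Two-sample normal formula: 2 × (14 × (1.96 + 0.84)/6)² gives 86 per arm after rounding up. Design effect 1 + 24 × 0.05 = 2.2. Total 2 × 86 × 2.2 = 378, against 25 × 15 = 375. The figure reproduces, and no stratification factor enters it.

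**Balance in Table 1.** Intervention 2 + 1 + 2 + 2 = 7 practices; control 1 + 3 + 2 + 2 = 8.
- High nurse volume: (1 + 2)/7 = 42.9% against (3 + 2)/8 = 62.5%, difference -0.196.
- High training participation: (2 + 2)/7 = 57.1% against (2 + 2)/8 = 50.0%, difference +0.071, about as even as 7 against 8 allows.

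The unevenness lies in the two low-training strata.

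**Shift in the estimate.** If high volume changes PAM by b points, over and above what baseline PAM captures, the intervention effect shifts by -0.196b.

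| b (assumed) | Shift | Share of the 6-point target |
|---|---|---|
| 2 | -0.39 | 6.5% |
| 4 | -0.79 | 13% |
| 6 | -1.18 | 20% |

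The direction depends on the sign of b, which is unknown. For training the shift is +0.071b, or 0.14 to 0.43 points over the same range.

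**Precision and power.** Evaluable patients per practice: 50 × 0.67 = 33.5. Variance of a practice mean: 196 × 0.05 + 196 × 0.95/33.5 = 9.80 + 5.56 = 15.36, of which 9.80/15.36 = 64% is between practices.

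Without the factors, the variance multiplier for the arm contrast is 1/7 + 1/8 = 0.268. SE = √(15.36 × 0.268) = 2.03, and 6/2.03 = 2.96. With a noncentral t on 13 df, power is 78.1%. This is below 80% despite more than 25 per practice because a t reference on 13 df replaces the normal approximation; the same t calculation at 25 per practice gives 73.3%.

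With both factors as main effects, the multiplier is the arm element of the inverse of X′X, where X holds an intercept, arm, training and volume for the 15 practices of Table 1. It equals 0.280, and 0.280/0.268 = 1.044 (unrounded inputs). The df are 15 - 4 = 11. If the factors explain a share r of between-practice variance, a practice mean has variance 9.80(1 - r) + 5.56.

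| r (assumed) | Variance of a practice mean | SE | Power, 11 df |
|---|---|---|---|
| 0 | 15.36 | 2.07 | 75.1% |
| 0.11 | 14.28 | 2.00 | 78.0% |
| 0.20 | 13.40 | 1.94 | 80.5% |
| 0.30 | 12.42 | 1.86 | 83.4% |

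Break-even with 78.1% is at r of about 11%. At r = 30% the SE ratio is 1.86/2.03 = 0.92, a fall of about 8%. Full stratum indicators cost more: 10 df and a multiplier ratio of 1.09.

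These figures treat the 15 practices as independent and of equal size, and ignore the baseline covariate.

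**The case against.** The strongest reply is that the article only outlines an a priori analysis plan that is not shown, so the factors may be in it. That has force where the article is silent. A reader might infer that the process-outcome models omit the factors too, but the article names no covariates for them, so omission cannot be established. It has less force for the primary model, whose covariate is stated, and for the secondary models, whose covariates are enumerated. Even if that list is read as covering the primary analysis, neither factor is in it.

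A reader might also infer that the allocation is unbalanced on both factors. It is not: training is 4/7 against 4/8. The nurse-volume gap would nearly vanish if one practice moved, and the counts may partly reflect the two practices that were randomised as a pair.

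Third, baseline PAM-13 is already in the model, and the training (2011) and staffing precede the trial. Part of any effect may already show in baseline scores. What counts is the share of variance the factors explain after baseline adjustment. The documents do not give it, and it could lie below 11%, in which case the adjustment costs power. This objection stands in full.

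**Conclusion.** The point holds for the primary PAM-13 model and the listed secondary models: the trial randomised on two factors it considers influential, and the stated models use neither. The possible distortion is modest, about 0.2 PAM points for each point of nurse-volume effect not captured by baseline PAM, and its direction is unknown.

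It would be wrong to infer that the omission inflates the false-positive rate. If the factors are prognostic, the overstated standard error is conservative, and the threat is to power. Nor do the documents support a claim that adjustment is sure to gain power. Under the plan's SD, ICC and effect, the change ranges from a loss of 3 points (factors explain nothing) to a gain of about 5 points (they explain 30%).

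The case for adjustment rests on agreement between analysis and design and on the uneven nurse volume, with a power gain as a conditional benefit. It does not invalidate the trial, but it should be corrected.

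**What to change.** Add training participation (high/low) and nurse volume (high/low), dichotomised as for the randomisation, as fixed main effects in the primary PAM-13 model and in the listed secondary models. Keep the model without them as a sensitivity analysis. Prefer main effects to stratum indicators, which use 3 df rather than 2. If the full analysis plan already contains the factors, state so and align the published outline. The process-outcome models should be checked against that plan.

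No new data are needed, since both variables were used to randomise every practice. The article reports that recruitment was still under way at submission, so the change could be written in before outcomes were complete. The statistical cost is 2 practice-level degrees of freedom (13 to 11) and a 4% variance inflation, which together amount to about 3 points of power if the factors turn out to explain nothing.

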### Patients

The population of chronically ill patients in the practices consists of approximately 9,100 patients with cardiovascular risk, 3,900 diabetes mellitus patients, 1,500 asthma patients and 900 COPD patients. These patients are regularly seen by the practice nurse. Patients can be included if they are over 18 years of age, have at least one of these chronic conditions and have a checkup appointment with the practice nurse in the inclusion period. Practices will send invitations with information about the study and informed consent forms to patients to participate in the study approximately 4 weeks before the planned checkup appointment of the patient. Patients will be given the option to fill in the questionnaires either digitally through the Internet or on paper. Participating patients will be asked to fill in an evaluative questionnaire one week after their consultation, and the final questionnaire after 6 months.

Medical-record data extraction will be performed by the data management agency of the care group. They can provide anonymous data on the participating patients from the research period. The research team will perform medical-record data analysis. The flow chart of the trial is shown in Figure 2.

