### Limitations of this study

This study is carried out in the DOH care group. This care group consists of group practices in primary care, and has an innovative mindset. Therefore, the implementation of SeMaS in other general practices will need guidance from experts. Also, implementation in other practices will need to be evaluated. Recruitment bias may be caused by the response of patients with certain characteristics, including current self-management status, and health literacy. Due to privacy legislation, it will not be possible to analyze the characteristics of non-responders.

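### The primary PAM-13 model names only baseline PAM-13 as a covariate; the listed patient covariates are not clearly applied to it and should be, at pre-intervention values

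*Protocol article*

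**What the plan says.** All references are to the protocol article.

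- **Analysis, PAM-13 model.** The ANCOVA is explained as "multilevel linear regression with the follow-up score as the outcome and the baseline score as a covariate". No further covariate is named in that paragraph.
- **Analysis, next paragraph.** It opens with "Each secondary outcome will be analyzed with a multilevel multivariate covariance regression model" and continues "Covariates that will be controlled for are: age, gender, chronic condition", followed by social support from the SeMaS, a depression diagnosis by ICPC code, health literacy by S-TOFHLA, and the baseline scores. The following sentence concerns the software for all analyses.
- **Analysis, opening.** A fuller plan is said to exist: "We made an *a priori* analysis plan for the primary analysis of the data, including details about the primary and secondary outcomes, covariates". The article gives its outline.
- **Practices.** "After performing the randomization procedure, we informed the practices about participation in the study".
- **Patients.** Invitations come from the practices and are timed to a scheduled nurse visit: "Practices will send invitations with information about the study and informed consent forms to patients to participate in the study approximately 4 weeks before".
- **Limitations of this study.** "Recruitment bias may be caused by the response of patients with certain characteristics, including current self-management status, and health literacy". The same section says that non-responders cannot be characterised.

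**The concern.** The covariate list stands under the secondary outcomes and repeats baseline adjustment, which the PAM-13 paragraph had already given for PAM-13. The natural reading is that PAM-13 is adjusted for its own baseline and the secondary outcomes for the whole list.

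The design makes the choice matter. Patients enter after their practice has been allocated, and the practice sends the invitations. Intervention staff are trained before the trial starts, so they can know their arm, and only intervention patients receive feedback on their profile. Patient mix could therefore differ between arms for reasons other than chance.

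Of the two traits named as sources of selective response, current self-management status is largely what baseline PAM-13 captures: the Background section describes PAM-13 as measuring the current level of self-management. Health literacy is measured at baseline but appears only in the list whose scope is unclear. If it differs between arms and predicts follow-up PAM-13 given baseline PAM-13, a baseline-only model leaves that difference in the treatment estimate. Two possible readings of the primary model also leave room to choose between estimates once the data are known.

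**Working it through.** **Inputs from the protocol.** Difference 6, SD 14.0, ICC 0.05, power 80%, alpha 0.05, 25 evaluable patients per practice, 15 practices (Sample size). Table 1 sums to 2+2+1+2 = 7 intervention and 1+2+3+2 = 8 control practices.

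**Step 1: reproduce the plan's figure.** Taking 6% as 6 PAM points and a two-sided test:
- n per arm = 2 × (14 × (1.96 + 0.842) / 6)² = 85.5, so 86.
- Design effect = 1 + (25 − 1) × 0.05 = 2.2.
- Total = 2 × 86 × 2.2 = 378, or 25.2 per practice. The stated 25 is reproduced.

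**Step 2: standard error.** SE = 14 × √(2.2 × (1/175 + 1/200)) = 2.149 points. Normal-approximation power for 6 points is 79.7%.

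**Step 3: chance imbalance.** Assume that a covariate also has ICC 0.05.
- At 25 per practice, the SD of its between-arm difference is √(2.2 × (1/175 + 1/200)) = 0.154 SD.
- With an assumed coefficient of 0.2 SD per SD given baseline PAM-13, this is 0.154 × 0.2 × 14 = 0.43 points.
- At 33 per practice: √(2.6 × (1/231 + 1/264)) = 0.145 SD, and 0.145 × 0.2 × 14 = 0.41 points.

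This is the spread of a random error with mean zero. At 25 per practice its share of the variance is 0.43² / 2.149² = 4%, and it is already inside the standard error.

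**Step 4: precision gained by adjusting.** In units of total variance, the variance of a practice mean is 0.05 + 0.95/25 = 0.088. The patient-level part is 0.038/0.088 = 43% of it.
- If the covariates remove an assumed 10% of patient-level variance, SE = 2.149 × √(1 − 0.043) = 2.10, about 2% lower.
- If they remove 5%, SE = 2.149 × √(1 − 0.0216) = 2.13, about 1% lower.
- If they remove 10% at both levels, SE = 2.149 × √0.90 = 2.04 and power is 83.7%.

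**Step 5: systematic imbalance, illustration only.** The documents give neither a covariate–outcome correlation nor an expected imbalance. Approximate bias from one covariate = partial r × imbalance in SD × residual SD. Assumed ranges: partial r 0.1 to 0.3; imbalance 0.1 to 0.5 SD; baseline PAM-13 explaining 0 to 50% of variance, so residual SD 14 down to 14 × √0.5 = 9.9.
- Lowest: 0.1 × 0.1 × 9.9 = 0.1 points.
- Highest: 0.3 × 0.5 × 14 = 2.1 points. This needs baseline PAM-13 to explain nothing.

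| Bias (points) | Two-sided type I error, SE held at 2.15 |
|---|---|
| 0.4 | 5.4% |
| 0.8 | 6.6% |
| 1.4 | 10% |
| 2.1 | 16% |

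**The case against.** **The text does not say that PAM-13 is adjusted for baseline alone.** The words on the baseline score explain what is meant by ANCOVA and need not be a closed list. The covariate sentence is not expressly limited to secondary outcomes, and the next sentence covers all analyses. The fuller plan is said to give covariates for the primary analysis. This stands in part: a reader might infer that the covariates are definitely excluded, and the document does not establish that. But the article does more than leave the matter to the plan. It states a covariate for PAM-13 and places the others under a different heading sentence, so the wording needs correcting on either reading.

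**Differential recruitment is not shown.** A reader might infer that the protocol concedes bias between the arms. It does not. The limitation concerns who responds, not response that differs by arm. Invitations are tied to planned checkups, both arms share one inclusion period, and no discretionary selection of patients is described. This stands. The design makes a difference by arm possible, not demonstrated.

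**Chance imbalance is not bias.** A reader might take the 0.41 to 0.43 points of Step 3 as a distortion of the result. It is random error that the multilevel standard error already reflects. This stands in full.

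**Baseline-only ANCOVA is a valid primary model, and a fuller one depends on complete covariate data.** Both are true. They argue for a missing-data rule and a retained baseline-only analysis, not for leaving the model unclear.

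**Conclusion.** The point holds in a limited form. As written, the primary PAM-13 model has one named covariate, and the remaining covariates are not clearly applied to it. Because practices invite patients after allocation and health literacy is a named source of selective response, measured differences that act beyond baseline PAM-13 could remain in the primary estimate.

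The size of such bias cannot be derived from the documents. The range of 0.1 to 2.1 points per covariate rests wholly on assumed correlations and imbalances, with the upper end at an extreme of those assumptions. The precision gain is about 1 to 2% of the standard error if only 5 to 10% of patient-level variance is explained. Adjustment would not remove selection on unmeasured traits.

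This does not invalidate the primary analysis. The change is worth making because it is nearly free, uses covariates already chosen and collected, and settles which model is primary.

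**What to change.** In the Analysis section, state that the primary PAM-13 model is a multilevel ANCOVA with baseline PAM-13 plus the covariates already listed, all at pre-intervention values:

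- social support from the T0 SeMaS;
- health literacy from the T0 S-TOFHLA;
- depression diagnosis coded before baseline;
- age, gender and chronic condition as at baseline.

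The timing needs stating because SeMaS and S-TOFHLA are repeated at 6 months (Figure 2 legend) and intervention nurses are asked to work on low social support. A follow-up value could itself be affected by the intervention.

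Keep the model with baseline PAM-13 alone as a prespecified sensitivity analysis.

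The cost is a few sentences and no new data. The terms are patient-level and use almost no practice-level degrees of freedom. The one real downside is that the primary result then depends on further questionnaire and record data, so a rule for missing covariate values must be set in advance. If the fuller analysis plan already fixes the primary covariates, the article's wording should be brought into line with it.
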